### Sample size

Sample size was calculated using resources available at the Laboratory of Epidemiology and Statistics (LEE) website of the Dante Pazzanese Institute (http://www.lee.dante.br/pesquisa/amostragem/qua_2_medias.html). The calculation was based on data provided by Sönmezer et al. [48]. In that article, Sönmezer et al. detected a significant difference in the serum levels of AMH in the first month after surgery, with a measurement of 2.72 ± 1.49 for the patients who received the hemostatic matrix versus 1.64 ± 0.93 for the patients who received bipolar coagulation. Here, we assume that the standard deviation in the AMH measurement of 1.49 in the first month was significant, since that was the number that generated the largest sample size when compared with other values from that article. The difference to be detected is 1.08, which corresponds to the mean difference in AMH in the first month between the patients who receive hemostatic matrix and those who receive bipolar coagulation. On those grounds, and for a statistical power of 80% (*p* = 0.05), each group would have to have 23 participants. Considering possible losses, the sample will be increased by 20% to 28 participants per group, making a total of 84 women. It should be noted that the present sample maybe not detect a powerful difference in treatment arms, but relevant contributions are expected.

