#### Data processing and analysis

The data will be double-entered by two different data entry operators, using the Epi Info software program, version 7.2. The two databases will be compared using the Validate function of the Epi Info software program. Statistical analysis will be conducted using the Microsoft Excel software and the SPSS statistical software package for Windows, version 19.0.0. The data entry operators and the statistician will be blinded in that they will receive the data marked simply as A, B, or C and will be unaware of which procedure corresponds to which letter. A significance level of 5% will be determined for all the statistical tests.

To analyze the numerical variables AMH and AFC, the Kolmogorov–Smirnov test of normality will be used to determine the type of analysis to be performed. If distribution is normal, two-way analysis of variance (ANOVA) will be used, with the group representing an independent factor (bipolar energy × suture × hemostatic matrix). Another factor to be analyzed will be paired time points (before surgery × 1 month × 3 months × 6 months). If distribution is not normal, non-parametric tests will be used to analyze the variables.

The Kruskal–Wallis test will be used to compare variables between the three groups at each time point, with Tukey’s multiple comparison test being used when comparisons are statistically significant. The Friedman test will be used to perform intra-group comparisons at the four evaluation moments, with Tukey’s multiple comparison test being used when they are significant.

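### In the non-parametric branch, three-arm pairwise comparisons are both gated by Kruskal–Wallis and Tukey-corrected; with three arms this is conservative and costs roughly 1–10 points of power

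*Protocol article*

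**What the plan says.** Protocol article, Data processing and analysis. A Kolmogorov–Smirnov test decides the route for AMH and AFC. Normal data go to two-way ANOVA, for which no pairwise procedure is named. Otherwise, "If distribution is not normal, non-parametric tests will be used to analyze the variables". On that route a Kruskal–Wallis "test will be used to compare variables between the three groups at each time point". Pairs of arms are then examined by Tukey's procedure, this "multiple comparison test being used when comparisons are statistically significant". The article does not say whether Tukey is applied to ranks or to measured values. Within arms, "The Friedman test will be used to perform intra-group comparisons at the four evaluation moments", again followed by Tukey. The level is common to all tests: "A significance level of 5% will be determined for all the statistical tests".

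Protocol article, Sample size. The trial is sized on one pair of arms. "The difference to be detected is 1.08", described as the "mean difference in AMH in the first month between the patients who receive hemostatic matrix and those who receive bipolar coagulation". With SD 1.49 and 80% power this gives 23 per group, raised to 28 for losses. No allowance is made for a global test in front of the pairwise test, or for a multiplicity correction after it.

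**The concern.** A pair of arms can be declared different only if the three-arm test is significant and the pair also exceeds Tukey's wider critical value. Either step can serve as the familywise safeguard for three arms. Using both holds the one contrast the trial was sized for to a stricter standard than the chosen 5% requires.

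The stake is a missed difference. The article's Discussion says that if the methods do not differ significantly, surgeons may choose among them by convenience and availability, so an avoidable non-significant result would feed a practical message. The Sample size section already admits that the sample may be too small to show a difference.

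**Working it through.** **1. The plan's own figure.** n per group = 2(z_α + z_β)²(SD/difference)², with SD 1.49 and difference 1.08, so (1.49/1.08)² = 1.903.
- One-sided 5%: 2 × (1.645 + 0.842)² × 1.903 ≈ 23.5. This is close to the stated 23.
- Two-sided 5%: 2 × (1.960 + 0.842)² × 1.903 ≈ 29.9, so 30.
- Inflation: 23 × 1.20 = 27.6, so 28; 3 × 28 = 84.

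**2. Why the gate is enough with three arms.** There are three pairwise null hypotheses: matrix = bipolar, matrix = suture, suture = bipolar. Any two of them imply the third. So either all three are true or at most one is.
- All true: a false pairwise claim needs a significant Kruskal–Wallis test, which has probability of at most 5%.
- One true: a false claim needs that pair's own test to reject, which has probability of at most 5%.

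The gated, unadjusted rule is therefore a closed test for one outcome at one visit. The pair test must itself be valid at 5%. A rank-sum test on the two arms' own ranks meets this when the null is equality of distributions.

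**3. Familywise error by simulation** (60,000 runs, SD 1.49 in every arm, 23 and 28 per arm; Monte Carlo standard error at 5% is √(0.05 × 0.95/60,000), about 0.09 points).

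| Rule | All arms equal | One arm different |
|---|---|---|
| Gate, then rank-sum at 5% | 4.7–4.9% | 4.7–5.0% |
| Gate, then rank-sum at Tukey cut-off | 4.0–4.1% | 1.7–1.8% |
| Gate, then Tukey on joint ranks | 4.3% | at most 1.5% |
| Rank-sum at 5%, no gate | 12.2% | 4.9–5.0% |

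**4. Power for matrix versus bipolar** (40,000 runs; means 2.72 and 1.64, SD 1.49 in all arms). The suture mean is assumed: 1.64 (equal to bipolar), 2.18 (midway) or 2.72 (equal to matrix). A = gate then rank-sum at 5%; B = gate then rank-sum at Tukey cut-off; C = gate then Tukey on joint ranks. All entries are in %, and losses are in points.

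| Data | n | Suture | A | B | C | A−B | A−C |
|---|---|---|---|---|---|---|---|
| Normal | 23 | = bipolar | 57.7 | 47.4 | 47.6 | 10.3 | 10.1 |
| Normal | 23 | midway | 51.8 | 46.6 | 47.9 | 5.2 | 3.9 |
| Normal | 23 | = matrix | 58.0 | 47.6 | 48.0 | 10.4 | 10.0 |
| Normal | 28 | = bipolar | 68.2 | 58.1 | 58.2 | 10.1 | 10.0 |
| Normal | 28 | midway | 61.8 | 57.0 | 58.1 | 4.8 | 3.7 |
| Normal | 28 | = matrix | 68.3 | 58.1 | 58.2 | 10.2 | 10.1 |
| Lognormal | 23 | = bipolar | 89.0 | 81.3 | 82.2 | 7.7 | 6.8 |
| Lognormal | 23 | midway | 84.5 | 81.0 | 82.6 | 3.5 | 1.9 |
| Lognormal | 23 | = matrix | 88.8 | 81.4 | 80.4 | 7.4 | 8.4 |
| Lognormal | 28 | = bipolar | 94.9 | 89.6 | 90.5 | 5.3 | 4.4 |
| Lognormal | 28 | midway | 91.4 | 89.2 | 90.3 | 2.2 | 1.1 |
| Lognormal | 28 | = matrix | 94.3 | 89.5 | 88.6 | 4.8 | 5.7 |

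If the pairs are compared on measured values, pooled t against Tukey after the same gate, normal data with suture equal to a sized arm give a loss of 8.2–8.5 points (for example 58.4 − 50.0 = 8.4 at 23 per arm). With lognormal values the corresponding loss is 10.8–12.4 points.

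**5. The four-visit step.** The argument in step 2 fails with four levels, because several pairwise nulls can remain true when one level differs. In 20,000 runs with 28 patients and one visit different, a significant Friedman test followed by unadjusted paired t tests gave 12.1–12.4% familywise error. With Tukey it was at most 2.0%.

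**The case against.** The best defence is that the planned rule is valid. A global test followed by Tukey never exceeds 5% within an outcome and visit, and preferring a less conservative valid rule is a question of efficiency. That stands. A reader might infer from the double step that the error rate is wrong; the text does not support this.

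A reader might also take 8–10 points as the cost in general. That figure needs normal data, which the article sends to ANOVA, and a suture mean that the article never states. The Background does lean towards bipolar differing from both other methods, which makes suture equal to matrix plausible, but it gives no figure. With skewed data the loss is smaller, and power is much higher under either rank rule.

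Nor does the Tukey step protect nothing. When one arm differs, it keeps the error for the remaining true-null pair at about 1–2% rather than up to 5%. Across AMH and the AFC measures at four time points, where the article states no correction, that extra strictness has some value.

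Tukey without the gate would also remove the redundancy: on measured, normal values it gave familywise error of 5.0%. With suture midway it is about as powerful as the gated unadjusted test (52.7% against 52.0% for pooled t at 23 per arm). With suture equal to a sized arm it is less so (52.5–52.6% against 58.4–58.8%).

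Finally, the larger shortfall lies in the sizing. A single two-sided comparison has about 69% power at 23 per arm and 77% at 28 before any gate. With normal data, dropping Tukey does not restore 80%.

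**Conclusion.** The point holds as a modest, cheaply mended loss of efficiency, confined to the three-arm comparison in the non-parametric branch. With exactly three arms, the 5% Kruskal–Wallis gate followed by valid unadjusted 5% pair tests holds familywise error at 5% within one outcome and visit, so the second correction is not needed for that purpose.

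The Tukey step lost power in every scenario examined, by 1.1 to 10.4 points when done on ranks. The spread comes from the assumed suture mean and the shape of the data. All runs used a common SD of 1.49, although the source study quoted in the Sample size section has 0.93 for bipolar. If Tukey were run on raw skewed values, the loss against the rank-sum rule would be far larger (at 23 per arm with suture equal to bipolar, 89.0 − 58.3 = 30.7 points). Most of that is the cost of a parametric test on skewed data, which is a separate matter.

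The conclusion must not be carried to the Friedman comparisons, where an adjustment is needed.

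**What to change.** In Data processing and analysis, replace the Tukey step after Kruskal–Wallis with a sentence to this effect: after a significant three-arm test at 5%, each pair of arms is compared by a two-sample rank-sum test on the ranks of those two arms, at 5% and without further adjustment (closed test for three groups). Keep a multiplicity correction for the four-visit comparisons within arms.

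The cost is one sentence and no patients. The downside to record is that, when the third arm differs, the false-claim rate for a single true-null pair rises from about 1–2% to at most 5%. Error across outcomes and visits remains uncontrolled, as it is now. The change should be made before the A, B and C codes are broken; the Trial status section reports 32 of the planned 84 randomized at the time of writing.

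### If AMH or AFC fails the normality test, change after surgery is tested only arm by arm, so the question whether surgery harms the ovary regardless of technique has no pooled test and no rule for combining three verdicts

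*Protocol article*

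**What the plan says.** The Discussion of the protocol article lists two questions: whether bipolar energy is responsible for ovarian damage, and whether surgery is responsible whichever technique is used. The abstract's Discussion raises the same alternative.

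The section Data processing and analysis sets two routes. A test on the data chooses between them: "the Kolmogorov–Smirnov test of normality will be used to determine the type of analysis to be performed".

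- **Normal route.** A two-way ANOVA with group as one factor. Time is the second: "Another factor to be analyzed will be paired time points (before surgery × 1 month × 3 months × 6 months". This model contains a time effect averaged over the three arms.
- **Rank route.** Between arms: "The Kruskal–Wallis test will be used to compare variables between the three groups at each time point". Over time: "The Friedman test will be used to perform intra-group comparisons at the four evaluation moments". Tukey comparisons follow where these are significant.

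On the error level: "A significance level of 5% will be determined for all the statistical tests". No sentence says which result, or which combination of results, answers the second question.

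**The concern.** The second question is about surgery across techniques. On the rank route nothing tests change across techniques. Kruskal–Wallis at a visit compares levels between arms at that visit and says nothing about a fall from before surgery. The within-arm Friedman tests are the only tests of change, and there are three of them per variable. The plan does not say whether all three must be significant, whether one suffices, or whether some pooled result decides. A normality test therefore determines whether the question meets one pooled time effect or three separate verdicts.

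If every arm falls by the same true amount, three tests in 23 to 28 women each can easily give one or two significant arms. That leaves the second question without an answer. It also produces a pattern (significant with one technique, not with another) that looks like evidence on the first question, although separate p-values do not compare arms. The Discussion says the results may guide surgeons' choice of method.

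**Working it through.** **1. What the sample size covers.** Inputs from Sample size: "The difference to be detected is 1.08", SD 1.49, and "for a statistical power of 80% (*p* = 0.05), each group would have to have 23 participants". The formula is n = 2(z_α + z_β)² SD² / difference².

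- One-sided 5%: 2 × (1.645 + 0.842)² × 1.49² / 1.08² = 23.5, close to the stated 23.
- Two-sided 5%: 29.9, that is 30.
- Inflation: 23 × 1.2 = 27.6, giving the stated 28 per arm and 84 in all.

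Sidedness is not stated. What matters here is that the calculation concerns a difference between two arms at one month. It gives no expected fall within an arm and no within-woman correlation, so it offers no assurance about the power of a within-arm Friedman test.

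**2. Conflict when the truth is the same in every arm.** Let p be the power of each within-arm test. One or two of the three are significant with probability 1 − p³ − (1 − p)³.

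| Per-arm power | Verdicts conflict | All three significant (p³) |
|---|---|---|
| 30% | 63% | 3% |
| 50% | 75% | 13% |
| 70% | 63% | 34% |
| 80% | 48% | 51% |
| 90% | 27% | 73% |
| 95% | 14% | 86% |
| 99% | 3% | 97% |

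With no fall at all, the chance of at least one significant arm is 1 − 0.95³ = 14%.

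**3. Simulation.** Four visits, SD 1.49, normal data with equal correlation between visits, the same fall in all arms, and a Friedman test per arm at 5%. The falls, correlations and profiles are assumptions. Falls of 0.54, 0.75 and 1.08 are 0.36, 0.50 and 0.72 SD. Cells give the share of trials with conflicting arm verdicts.

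| Setting | Fall 0.54 | Fall 0.75 | Fall 1.08 |
|---|---|---|---|
| 23 per arm, sustained, correlation 0.5 | 61% | 74% | 36% |
| 23 per arm, sustained, correlation 0.7 | 76% | 54% | 6% |
| 23 per arm, sustained, correlation 0.8 | 69% | 23% | 0.4% |
| 23 per arm, sustained, correlation 0.9 | 20% | 0.5% | 0% |
| 23 per arm, half recovered by month 6, correlation 0.7 | 68% | 69% | 21% |
| 28 per arm, sustained, correlation 0.7 | 73% | 35% | 2% |

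Over falls of 0.3–0.4 SD, correlations of 0.6–0.8, both profiles and both sample sizes, conflict occurs in about 41–75% of trials.

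**4. A pooled test on the same data.** With 23 per arm, correlation 0.7 and a sustained fall of 0.54, one Friedman test over all women has 94.5% power, against 46.5% per arm. If half the fall has recovered by month 6, the pooled Friedman test keeps 85.3%. A pooled paired contrast from baseline to month 6 has 96.7% power for the sustained fall but 49.6% with recovery. The choice of visit therefore matters, and the Background itself expects the decrease to recover over the following months.

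**5. What a pooled test cannot show.** Let one arm alone have a sustained fall of 0.72 SD, with 23 per arm and correlation 0.6–0.8. A pooled test (Friedman or month-6 paired) is then significant in about 41–81% of trials, although the damage is specific to one technique. All three Friedman tests are significant in under 1%. A direct between-arm comparison of change over all visits detects the difference in 94–100%.

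The lower end can be checked by hand at correlation 0.6. The change from baseline to the mean of three later visits has variance (4/3)(1 − 0.6) = 0.533 in SD² units. The noncentrality is 23 × (2/3) × 0.72² / 0.533 = 14.9 on 2 degrees of freedom, which gives power of about 94%. Change to one visit only has variance 2(1 − 0.6) = 0.80 and noncentrality 9.9, which gives about 80%. A single-visit comparison is thus less sensitive than one using all visits.

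**The case against.** Four points can be made for the plan as written.

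*Testing each arm is a fair reading of the question.* To say that surgery harms the ovary whichever technique is used, one may require a fall in every arm, and three tests that must all pass would do that. This stands in part. A reader might infer that the question simply needs one pooled contrast. It does not, because step 5 shows that one damaged arm can carry a pooled test. But the all-must-pass rule is not stated, and its power is only 51% when each arm has 80%.

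*The conflict rate depends on assumed values.* This stands. A reader might infer that conflict is to be expected in this trial. The documents give no within-arm fall and no correlation. At a sustained fall of 0.72 SD with 28 per arm, conflict occurs in only 0–9% of trials over correlations of 0.6–0.8. With partial recovery the figure is 1–27%.

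*No misreading is planned.* This also stands. A reader might infer that the trial will compare techniques through separate within-arm p-values. The plan says no such thing, and its between-arm comparison is a direct one, by Kruskal–Wallis. The risk is that a mixed set of verdicts invites the misreading and nothing guards against it.

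*Linking questions to tests can be left to a fuller document, and the ANOVA route already has a pooled effect.* The second half is correct and limits the point to the rank route, although the ANOVA time effect is not designated as the answer either. The first half does not dispose of the point: the article names the test and fixes it within arms, and that stated choice does not match a stated question.

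**Conclusion.** The point holds for the rank route. There, change over time is tested only by three within-arm Friedman tests with no combining rule, while the ANOVA route offers a pooled time effect. Given equal true falls and per-arm power of about 30–80%, the arm verdicts conflict in roughly half to three quarters of trials. For sustained falls of about 0.7 SD or more with high correlation, conflict is rare. These sizes rest on an assumed fall, correlation and recovery profile.

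The rank route is a realistic prospect. In the AMH figures under Sample size the SD is about 55% of the mean (1.49/2.72 = 0.55; 0.93/1.64 = 0.57), which suggests skewed data, though that is an inference and not something the documents state.

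This should be corrected before analysis. It does not undermine the between-arm comparison of techniques.

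**What to change.** In Data processing and analysis, for both routes:

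1. **Test before-after change once over all arms at 5%.** Use either a pooled time test over the four visits (the ANOVA time effect, or Friedman over all women) or a paired contrast from baseline to one visit named in advance. If a single visit is used, choose it in view of the recovery that the Background expects, and not month 6 by default.
2. **Compare change from baseline directly between arms.** Use the group-by-time term, or Kruskal–Wallis on the change. Conclude that damage does not depend on technique only from the pooled result read with this comparison and with arm-specific changes and their 95% confidence intervals. A non-significant between-arm result alone does not show equal damage.
3. **Add a reading rule.** Significance in one arm and non-significance in another will not be taken as a difference between techniques.

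The cost is a few sentences and no new data. The per-arm Friedman tests become supportive, which is a small loss. Trial status reports 32 of 84 women randomized at 24 April 2019, so at that date there was time to make the change before analysis.

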Ata et al. recently conducted a meta-analysis that included six studies, four of which consisted of randomized clinical trials (RCT). Of these, two included only patients with bilateral endometriomas, a situation that is known to be associated with an increased risk of impaired ovarian function compared to unilateral endometriomas, irrespective of the hemostatic technique. Furthermore, the investigators concluded that the quality of the evidence in the studies analyzed in that meta-analysis was moderate and that it would be advisable to avoid the use of bipolar energy whenever possible. In view of the small magnitude of the effect, the possible side effects and the additional cost of hemostatic agents, it is not possible to recommend substituting bipolar coagulation with another method. Indeed, those investigators suggested that further RCTs should be conducted to compare different hemostatic techniques [13].

Another meta-analysis included some widely heterogenous studies that compared laparoscopy with laparotomy, used different methods for the evaluation of ovarian function, and included cases of bilateral endometriomas. The authors suggested that new clinical trials should be conducted to compare different hemostatic methods in order to provide further clarification [12].

Notably, none of the studies in which bipolar coagulation was evaluated provided details on how the bipolar energy was used, stating only the voltage that was applied. Therefore, there are no precise data on how many points were coagulated or for how long cauterization was performed.

There are also controversies in relation to the methods used to evaluate ovarian function. The most commonly used methods are measuring anti-Müllerian hormone (AMH) and follicle-stimulating hormone (FSH) levels and performing antral follicle count (AFC) by ultrasound. Some studies have found AMH to be the most accurate, since this method provides a systemic evaluation with little variation during the menstrual cycle. Other studies have indicated AFC as the best method, since evaluation is performed specifically on the affected ovary, without the effect of any possible compensation by the contralateral ovary. Furthermore, some studies have shown a reduction or no change in AMH, while others have shown no change or even an improvement in AFC following the treatment of endometriomas [40–44].

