### Eligibility criteria

Women aged at least 18 years, with regular menstrual cycles (21–35 days) and a diagnosis of a unilateral ovarian cyst suggestive of an endometrioma, with an indication for laparoscopic surgery to remove the cyst due to pelvic pain, infertility, or persistence of the cyst will be eligible for the study. Exclusion criteria are: previous ovarian surgery; endocrine dysfunction (diabetes, thyroid disorders, hyperprolactinemia, adrenal disease, polycystic ovary syndrome); use of hormones in the past three months; suspected malignant ovarian tumor requiring oophorectomy; history of chemotherapy or radiotherapy; coagulation disorders; pregnancy; and autoimmune disease.

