### Procedures for the assessment of ovarian reserve

Ovarian reserve will be assessed by measuring AMH and by performing AFC using ultrasonography at four different moments: before surgery and one, three, and six months after surgery. Serum samples will be obtained from each participant and centrifuged for 10 min to separate the cell contents and debris. Each serum sample will be transferred to polypropylene tubes and stored at − 80 °C.

AMH levels will be quantitatively measured using enzyme-linked immunosorbent assay (ELISA) (Diagnostic Systems Laboratories, Webster, TX, USA), with a detection sensitivity of 0.006 ng/mL.

Transvaginal ultrasonography for antral follicle count will be performed during the early proliferative stage (days 3–7 of the menstrual cycle) and the total number of follicles with diameters < 10 mm will be considered.

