### Procedures for laparoscopic surgery

The same surgeon will perform all the surgical procedures, with the participants under general anesthesia and in a semi-lithotomy position. A 10-mm umbilical puncture will be performed for the camera after insufflation of the pneumoperitoneum. Three additional 5-mm punctures will be performed on the right iliac fossa, left iliac fossa, and suprapubic area to allow the instruments to be inserted. Intra-abdominal pressure will be maintained at approximately 15 mmHg.

Endometriosis will be classified according to the 1997 Revised American Society for Reproductive Medicine (ASRM) classification. In all the groups, endometriomas will be removed using traction-countertraction techniques. Adhesiolysis will be performed to separate the ovary from the adjacent structures, as necessary. In case of cyst rupture, the contents will be aspirated and the site of spillage will be thoroughly rinsed.

In the group allocated to receive bipolar coagulation, hemostasis will be performed using bipolar tweezers at 30 W as few times as possible, just to control any considerable bleeding. The number of coagulated points will be recorded and the duration of the procedure at each bleeding point will be measured. These parameters will help clarify any possible flaws in previous studies that failed to specify the number of coagulated points or the duration of coagulation at each point.

In the group allocated to receive hemostasis by laparoscopic suture, the procedure will involve simple intra-ovarian sutures (1 or 2 knots with 2–0 Vicryl) and the number of sutures will be counted.

In the group allocated to receive hemostasis by hemostatic matrix, the sealant will be applied on the ovarian wound surface.

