### Data collection, processing, and analysis procedures

#### Data collection instrument

A specific form will be developed for the study. It will be in the form of a handwritten log. Prospective data collection will be performed on the day of the intervention and subsequently for the data following the intervention. The follow-up items for the participants are presented in Table 1 and Fig. 2.

**Table 1 Tab1:** The standard protocol items and timing of the measurements

Measurements	T0	T1	T2	T3
Age, BMI, complaints, gynecological and obstetric history	x			
The largest cyst diameter	x			
Side of pathology	x			
Surgery: duration, blood loss, perioperative complications, ASRM classification	x			
Hemoglobin	x			
Bipolar coagulation (number of points coagulated)	x			
Suture (number of stitches sutured)	x			
Hemostatic (number of hemostatic used)	x			
AMH	x	x	x	x
AFC in affected ovary	x	x	x	x
AFC in the contralateral ovary	x	x	x	x
Total AFC	x	x	x	x

*BMI* body mass index, *T0* before surgery, *T1* one month after surgery, *T2* three months after surgery, *T3* six months after surgery

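### Affected-ovary follicle counts are taken with the endometrioma in place before surgery and without it afterwards, so a flat or rising before-after AFC cannot show that surgery does no damage

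*Protocol article*

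**What the plan says.** Under Eligibility criteria, each woman enters with "a diagnosis of a unilateral ovarian cyst suggestive of an endometrioma". Under Procedures for laparoscopic surgery, the cyst is taken out in every arm: "In all the groups, endometriomas will be removed using traction-countertraction techniques".

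Ovarian reserve is assessed by AMH and AFC "at four different moments: before surgery and one, three, and six months after surgery". The counting rule fixes the cycle days (3 to 7) and the size limit: "the total number of follicles with diameters < 10 mm will be considered". It does not mention an ovary with a cyst in it. Table 1 lists "AFC in affected ovary", contralateral AFC and total AFC at all four visits (T0 before surgery; T1, T2 and T3 after it).

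Under Data processing and analysis, the pre-surgery visit is one level of the time comparison in both branches. In the ANOVA branch: "Another factor to be analyzed will be paired time points (before surgery × 1 month × 3 months × 6 months". In the non-parametric branch: "The Friedman test will be used to perform intra-group comparisons at the four evaluation moments".

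The Discussion poses two questions. The second asks whether surgery itself causes ovarian damage, whichever hemostatic method is used.

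**The concern.** All three arms are operated on, so randomization cannot answer the second question. Only a comparison of before with after can. For the affected ovary, the conditions of counting change at exactly the point where that comparison is made. The planned tests make no allowance for this.

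The Background already carries a warning sign. After noting studies with a reduced or unchanged AMH, it continues: "while others have shown no change or even an improvement in AFC following the treatment of endometriomas". A flat or rising count after cyst removal is therefore a foreseeable result here. It could reflect no damage, real recovery, or real loss offset by better visibility, and neither planned test can tell these apart. A report that took it as reassurance would err towards missing harm.

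**Working it through.** The plan has no figure of its own to reproduce on this point; its sample size is built on AMH.

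**Inputs from the protocol article**
- One count before surgery and three after; cyst present at the first and removed before the rest, in every arm.
- 28 women per arm, or 23 before the allowance for losses (Sample size).
- 5% significance level (Data processing and analysis).

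**Assumptions (not in the documents)**
- v, the share of affected-ovary follicles that can be counted with the cyst in place: 0.6 to 1.0. Visibility after removal is taken as complete.
- L, the true loss of follicles: 0 to 40%.
- Mean affected-ovary count 6, with 5 and 8 as alternatives; Poisson counts with gamma variation between women (shape 4).

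**Step 1: apparent change.** With true mean count m, the expected count is v × m before surgery and (1 − L) × m after it. The apparent relative change is (1 − L)/v − 1.

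| True loss L | v = 1.0 | v = 0.9 | v = 0.8 | v = 0.7 | v = 0.6 |
|---|---|---|---|---|---|
| 0% | 0% | +11% | +25% | +43% | +67% |
| 20% | −20% | −11% | 0% | +14% | +33% |
| 30% | −30% | −22% | −13% | 0% | +17% |

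For example, L = 0.2 and v = 0.7 give 0.8/0.7 − 1 = +14%. Loss is hidden when v = 1 − L and appears as a gain when v is smaller still. At v = 1 there is no distortion.

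**Step 2: the planned Friedman test.** Simulated trials, four visits, one arm, true loss 30%. Entries are the share of trials with a significant fall.

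| Setting | v = 1.0 | v = 0.9 | v = 0.8 | v = 0.7 |
|---|---|---|---|---|
| 28 women, mean 6 | 74% | 39% | 13% | 2% |
| 28 women, mean 8 | 85% | not run | 18% | 3% |
| 23 women, mean 5 | 54% | not run | 10% | 2% |

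In the opposite case (no true loss, v = 0.7, 28 women, mean 6), about 74% of trials show a significant but false rise.

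**Step 3: what is and is not exposed.** Total AFC contains the affected ovary, so it carries a diluted form of the problem. With an assumed contralateral mean of 8, detection of a 30% affected-ovary loss through total AFC falls from 35% at v = 1 to 6% at v = 0.8. Contralateral AFC is counted in an ovary without the cyst throughout, and AMH is a serum measure; neither depends on seeing follicles around a cyst. T1 to T3 are alike among themselves. Between-arm comparisons at one visit are protected in expectation, because all arms have the cyst at T0 and none has it later.

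**The case against.** The strongest objection is that nothing in the article says an endometrioma lowers the visible count. That stands. Only the counting condition changes by design; a shift in the count itself is an assumption, and the simulated percentages show what follows if it holds. They are not evidence that it does.

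A reader might infer from the reported AFC improvements that the pre-surgery count must be too low, since stripping tissue cannot create follicles. The documents do not support that. AFC is a count at one visit, not a fixed stock. The Background cites studies in which the disease itself impairs ovarian function, and others in which the post-surgery decrease is temporary and tends to recover. A rise could be real.

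A reader might also infer that the second question rests on AFC alone, or that the protocol commits itself to reading an unchanged AFC as absence of harm. Neither is so. AMH is analysed over the same four visits, and the article's only stated reading of a null result concerns differences between methods. The trial's main aim, the comparison of techniques, is not touched.

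Finally, dropping the before-after AFC comparison would discard the only ovary-specific interval that spans surgery. AMH is no perfect substitute: the Background says it may reflect compensation by the other ovary and may already be lower before surgery in women with endometriomas. This argues for downgrading the comparison, not banning it.

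What remains is that the plan specifies a four-visit comparison as if the visits were interchangeable, and the planned test cannot separate visibility from loss or recovery.

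**Conclusion.** The point holds in a limited form. It is certain from the protocol that affected-ovary AFC is counted under different conditions at T0 and at T1 to T3, and that both analysis branches ignore this. It is not certain that the counts shift, or by how much. If visibility with the cyst in place is 0.9, 0.8 or 0.7, the chance of a significant fall after a true 30% loss drops from about 74% to about 39%, 13% and 2% (28 women per arm, mean count 6, full visibility after removal). A flat or rising affected-ovary or total AFC therefore cannot count as evidence that surgery does no damage. The correction is worth making, because it changes what the trial may conclude on its second question and needs no new data. It gives no ground to doubt the between-arm results.

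**What to change.** In Data processing and analysis:

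1. Name AMH as the primary basis for the before-after answer to the second Discussion question.
2. Keep the comparison of T0 with later visits for affected-ovary and total AFC as supportive only, and state that no change or a rise is not evidence against damage.
3. Report it beside contralateral AFC, the comparison among T1, T2 and T3, and a sensitivity analysis by largest cyst diameter.
4. Adjust between-arm AFC comparisons at T1 to T3 for T0 AFC and largest cyst diameter.

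Every variable is already in Table 1, so the cost is wording and a few extra analyses. At the stated trial status 32 of 84 women had been randomized, so the wording could be fixed before the final analysis. The price is that the before-after AFC p-value carries less weight and more rests on AMH. The limits of AMH (contralateral compensation and the endometrioma's possible effect on pre-surgery levels) should be stated with the result.
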